### Data management

CRF data will be entered into the data management system REDCap. REDCap holds standards according to the Danish Data Protection Agency (i.e. stored on private servers). In the CRFs and the database, participant identification will be replaced by a code, and a participant identification list will be kept safely, separate from the CRFs by the local investigator.

### Statistics

The intervention group and the control group will be compared concerning all outcomes based on the intention-to-treat principle. That is, all participants will be analysed in the groups to which they were randomized, regardless of whether they adhered to the allocated intervention.

In general, count data will be analysed using Poisson regression, continuous data with mixed linear modelling, and binary data with logistic regression. For the speech audiometry, we plan to dichotomize the data into an ≥8% decrease or not, to be able to apply logistic regression. For the AAO-HNS Functional Level Scale, we plan to dichotomize the outcome into a change ≥2 or not, for the same purpose.

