#### Secondary outcomes (main study 3 months)

The secondary outcomes of this study are comparisons between the two study groups regarding:Pure-tone audiometry of affected ear, four-tone average of 500, 1000, 2000, and 3000 Hz (dB)Pure-tone audiometry of affected ear, three-tone average of 125, 250, and 500 Hz (dB)Speech audiometry of affected ear, discrimination (%)AAO-HNS Functional level scale (1–6)Subjective hearing (0–10 arbitrary scale)The subjective intensity of ear fullness/pressure (0–10 arbitrary scale)The subjective intensity of dizziness/unsteadiness (0–10 arbitrary scale)The subjective intensity of tinnitus (0–10 arbitrary scale)Need of “escape medication”Number of subjects leaving the study because of treatment failureNumber of subjects satisfied with the treatmentSerious adverse events (as defined by the ICH-GCP)

These outcomes were chosen to assess any possible effects of treatment on hearing, functional level, and subjective symptoms.

The number of vertigo attacks, need for escape medication, and level of subjective symptoms will be recorded weekly by the study subject on a standardized form. Hearing tests will be performed at inclusion and after 3 months. A tympanometry will be performed after 1, 2, and 3 months. Assessment of AAO-HNS functional level scale will be made at inclusion and after 3 months. Menière’s disease staging (I–IV) will be decided at inclusion. Four-tone average of worst audiogram during the last 6 months: < 26 dB = Stage 1, 26–40 dB = Stage 2, 41–70 dB = Stage 3, > 70 dB = Stage 4. The equipment for hearing tests is maintained and calibrated by each study centre.

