### Sample size

The primary outcome in the study will be the number of attacks within the first 3 months after ventilation tube insertion. Because this is count data (i.e. an incidence rate) a Poisson distribution is expected, and a Poisson regression model most likely will give the best fit for analysis of the primary outcome.

The simulation software ”Powersim” developed for the used statistical package, STATA, was applied for Power calculations.

Given the lack of published data concerning the expected effect of ventilation tube insertion, we chose to assume a 50% reduction in the intervention group, which we believe is realistic as well as a necessity. A 50% reduction gives an Incidence Rate Ratio (IRR) of 0.5 and an ln(IRR) of −0.69315.

Using an alpha value of 0.05 and an expected effect size of 0.5 (ln(0.5) = −0.69315), and to obtain a power of 0.8, an expected 94 participants in total or 47 participants in each group will be necessary. To adjust for drop-outs, a safety margin of 10% results in 104 participants in total.

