#### Audiometric tests

The audiometric tests include pure-tone audiometry: an average of 500, 1000, 2000, and 3000 Hz and an average of 125, 250, and 500 Hz (dB), speech audiometry: single-syllable phonetically balanced word lists, speech discrimination (%), and tympanometry (to indicate function and patency of active tubes). The audiometric tests will be performed at inclusion and after 3 months. A tympanometry will be performed after 1, 2, and 3 months to objectively assess tube patency.

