**Table Tabc:** 

**Secondary outcome**	**Type of data**	**Analysis**
Pure-tone audiometry of affected ear, 4 tone average of 500, 1000, 2000, and 3000 Hz	Continuous	Mixed linear modelling
Pure-tone audiometry of affected ear, 4 tone average of 125, 250, and 500 Hz	Continuous	Mixed linear modelling
The subjective hearing	Continuous	Mixed linear modelling
The subjective intensity of ear fullness/pressure	Continuous	Mixed linear modelling
The subjective intensity of dizziness/unsteadiness	Continuous	Mixed linear modelling
The subjective intensity of tinnitus	Continuous	Mixed linear modelling
Number of subjects leaving	Count	Poisson-regression
Number of subjects satisfied	Count	Poisson-regression
The need for escape medication	Count	Poisson-regression
Serious adverse effects	Binary	Logistic regression
Speech audiometry	Binary data. Dichotomized to > 8% or < 8% decrease in speech audiometry	Logistic regression
AAO-HNS Functional Level Scale	Binary. Dichotomized to a change in > 2 or < 2 levels after 3-months follow-up	Logistic regression, alternatively linear regression with bootstrap

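### Cutting the speech discrimination score at an 8% decrease gives up power that the protocol's own mixed linear model would keep

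*Protocol article*

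**What the plan says.** The secondary outcomes list gives the measure as "Speech audiometry of affected ear, discrimination", in percent. The Audiometric tests section says it comes from "single-syllable phonetically balanced word lists, speech discrimination", again in percent. The timing is fixed by "Hearing tests will be performed at inclusion and after 3 months", so each participant has one score before treatment and one after.

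The Statistics section sets the general rule "continuous data with mixed linear modelling, and binary data with logistic regression". It then takes speech audiometry out of the continuous group: "For the speech audiometry, we plan to dichotomize the data into an ≥8% decrease or not, to be able to apply logistic regression". The secondary-outcome table repeats the cut as "Binary data. Dichotomized to > 8% or < 8% decrease in speech audiometry" and assigns it to logistic regression. The same table sends both pure-tone averages to mixed linear modelling. For the functional level scale, which is also dichotomised, it names a linear regression with bootstrap as an alternative. For speech audiometry it names none.

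The article does not say how many words a list has, what baseline scores are expected, why 8% was chosen, or whether 8% means percentage points or a relative fall.

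**The concern.** The score is numerical when collected, and the protocol has a model for numerical outcomes. Making it binary so that a binary model can be fitted is circular: the need for logistic regression arises only from the cut.

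Three things follow. First, information is discarded: falls of 8 and 40 points count the same, as do a fall of 6 points and a gain of 20, so power drops. Second, the rule looks in one direction only. An improvement is coded as no change, so a benefit can appear only as a smaller share of decreases. Third, a word-list score has sampling error. Eight points is 2 words of 25 or 4 words of 50, so a participant whose hearing has not changed may cross the cut by chance. At stake is how much this secondary outcome can tell us about whether the tube protects or harms speech understanding.

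**Working it through.** **Inputs from the protocol.** Cut: a decrease of at least 8% (Statistics), read here as percentage points. One score at inclusion and one at month 3. Alpha 0.05, taken as two-sided; 47 per arm (Sample size). The stated total reproduces as 94 × 1.1 = 103.4, rounded up to 104. That calculation is for the primary outcome; no power is stated for speech audiometry.

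**Assumed, because not stated.** List length of 25, 50 or 100 words; baseline distribution; SD of change; size of effect.

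**Step 1: loss from the cut, without assuming a list length.** Take change scores as normal with standard deviation SD. The difference with 80% power at 47 per arm as a continuous score is δ = (1.960 + 0.842) × SD × √(2/47). The share with a fall of at least 8 points is Φ((−8 − m)/SD) in the control arm, with mean change m, and Φ((−8 − m − δ)/SD) in the better arm.

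| SD | m | δ | Share worse | Power after cut | Per arm for 80% |
|---|---|---|---|---|---|
| 8 | 0 | 4.6 | 15.9% vs 5.7% | 35% | 146 |
| 10 | 0 | 5.8 | 21.2% vs 8.4% | 41% | 121 |
| 15 | 0 | 8.7 | 29.7% vs 13.3% | 49% | 98 |
| 20 | −5 | 11.6 | 44.0% vs 23.3% | 57% | 81 |

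Over SDs of 8 to 20 and control mean changes of 0 or −5, an effect with 80% power keeps 35 to 57%.

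**Step 2: simulation with word-list error.** 47 per arm; true baseline score with mean 70% and SD 15; individual true change with SD 8; true mean worsening of 8 points in one arm; binomial scoring at both visits. A Wald logistic test of the 8-point decrease is set against the month-3 score adjusted for baseline.

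| List | Cut | Continuous | Cut, baseline mean 90% (SD 8) | Continuous, baseline mean 90% (SD 8) |
|---|---|---|---|---|
| 25 words | 56% | 77% | 72% | 88% |
| 50 words | 72% | 90% | 84% | 96% |
| 100 words | 82% | 97% | 89% | 99% |

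Repeat runs agree within a few points. With no true effect, both methods reject in about 4 to 5.5% of trials.

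**Step 3: benefit instead of harm.** With a true 8-point improvement in one arm and baseline mean 70%, power is about 51 to 57% with the cut, against 78 to 97% for the continuous score, across the three list lengths.

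**Step 4: chance of being scored worse with unchanged hearing.** Two independent Binomial(n, p) scores with the same p have a difference with SD 100 × √(2p(1 − p)/n) points. For n = 25 and p = 0.70 this is 100 × √(0.42/25) = 13.0 points. A fall of at least 2 words, with continuity correction, starts at 6 points, and 1 − Φ(6/13.0) is about 32%, which agrees with the exact value.

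| True score | 25 words | 50 words | 100 words |
|---|---|---|---|
| 50% | 34% | 24% | 14% |
| 70% | 32% | 22% | 12% |
| 80% | 30% | 19% | 9% |
| 90% | 24% | 12% | 4% |
| 95% | 15% | 5% | 1% |

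The table's strict form (above 8) gives 12 to 24% with 25 words and 7 to 18% with 50 words, over true scores of 50 to 90%.

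**The case against.** A prespecified deterioration endpoint is a legitimate choice, and some readers prefer a proportion to a mean difference. This is one of twelve secondary outcomes; the primary outcome, the sample size and the superiority claim do not touch it. List length may well be given in the full protocol, so its absence from an article is no fault. The simulation also rests on a baseline mean, an SD and an effect that the documents do not supply.

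Much of this stands. It limits the point to a loss of efficiency in a secondary analysis, and it makes the chance-error figures conditional. It does not remove the loss, which appears at every list length and both baselines tried, and also in the calculation that needs no list length. Nor does the article defend the cut as a clinical endpoint; its only reason is the choice of model.

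A reader might go further and infer that the event is mostly measurement noise, that a null result would be uninformative, or that a gain cannot be seen at all. The documents do not support that. A dichotomy with 56 to 82% power in the main scenario is not uninformative. Chance crossings fall to about 5% or less at true scores of 95% and above with 50 words, and at 90% and above with 100 words. A gain would still appear indirectly as fewer decreases, and the two pure-tone averages and subjective hearing are analysed as continuous and can show improvement directly.

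**Conclusion.** The point holds as an avoidable loss of power on a secondary outcome. At 47 per arm, the cut costs about 15 to 21 percentage points of power against the baseline-adjusted score when the true effect is an 8-point worsening and mean baseline is 70%, and about 10 to 16 points when mean baseline is 90%. For a true improvement the loss is larger. These sizes depend on the stated assumptions; the direction of the loss was the same in every scenario tried.

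The statement that 12 to 34% of unchanged participants would be scored as worse holds only for lists of 25 to 50 words and true scores of 50 to 90%. This misclassification should be similar in both arms, so it dilutes a difference and does not create a false one. The planned comparison is valid but inefficient.

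**What to change.** In the secondary-outcome table, move speech audiometry to the continuous rows, and change the matching sentence in the Statistics section. Analyse the month-3 discrimination score with the mixed linear model planned for the pure-tone averages, adjusted for the inclusion score, and report the mean difference in percentage points with its interval. If scores are skewed or crowd the ceiling, use a bootstrap interval or a binomial model of words correct.

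Keep the 8% decrease as a supportive descriptive count, stated in percentage points and with one inequality throughout. At present the text includes a fall of exactly 8, while the table leaves it in neither group.

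The change needs no new data or visits. The cost is that the main result becomes a mean difference, which some clinicians find less direct than a proportion; the retained count meets that need.

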#### Inclusion criteria

Participants aged 18 years or older with definite or probable unilateral Menière’s disease according to the diagnostic criteria formulated by the Classification Committee of the Bárány Society, The Japan Society for Equilibrium Research, the European Academy of Otology and Neurotology (EAONO), the Equilibrium Committee of the American Academy of Otolaryngology – Head, and Neck Surgery (AAO-HNS), and the Korean Balance Society [16]:A.Two or more spontaneous episodes of vertigo, each lasting 20 min to 12 hB.Audiometrically documented low- to medium-frequency sensorineural hearing loss in the affected ear on at least one occasion before, during, or after one of the episodes of vertigoC.Fluctuating aural symptoms (hearing, tinnitus, or fullness) in the affected earD.Not better accounted for by another vestibular diagnosis

Furthermore, the patient must have experienced at least two vertigo attacks during the last 3 months before inclusion.

In probable Menière’s disease, the diagnostic criteria cover the same points (A, C, D). However, episodes of vertigo or dizziness may last from 20 min to 24 h [17]. Furthermore, the patients must have experienced at least two spontaneous vertigo attacks lasting more than 20 min during the past 3 months [16].

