#### Functional level scale

The AAO-HNS functional level scale (see Additional file 1: Appendix 5.1) consists of written descriptions of how Menière’s disease affects the life of the participants, from no impact at all (level 1) to handicapped and unable to work (level 6). The participant chooses the description that fits best. The form will be filled out at inclusion and after 3, 6, 12, 18, and 24 months.

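### The six-level functional scale is reduced to a two-level change so that logistic regression can be used; this discards one-level changes, leaves direction open, and sits beside a conflicting cut and an alternative analysis with no rule for using it

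*Protocol article*

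**What the plan says.** The AAO-HNS functional level is one of the secondary outcomes of the 3-month main study and is recorded at inclusion and at 3 months. It has six ordered levels (running "from no impact at all (level 1) to handicapped and unable to work (level 6").

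Two places in the protocol article fix its analysis:

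- Statistics, running text: "For the AAO-HNS Functional Level Scale, we plan to dichotomize the outcome into a change ≥2 or not, for the same purpose". The sentence before it, on speech audiometry, gives the purpose: "to be able to apply logistic regression".
- Statistics, Outcomes, secondary-outcome table: the type of data is "Binary. Dichotomized to a change in > 2 or < 2 levels after 3-months follow-up" and the analysis is "Logistic regression, alternatively linear regression with bootstrap".

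Neither place says whether change means improvement, worsening or both. The eligibility criteria set no minimum functional level. Entry depends on the diagnosis and on attack frequency: "the patient must have experienced at least two vertigo attacks during the last 3 months before inclusion".

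**The concern.** The reason given for the cut is that it makes a particular model usable. That reason does not require a cut, because proportional-odds logistic regression is designed for a short ordered scale.

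The cut has a cost. A patient who moves from level 5 to 4, or from 3 to 2, is scored like a patient who did not move. A patient who enters at level 2 and becomes symptom-free at level 1 is also scored as unchanged. If direction is ignored, a patient who gets two levels worse falls in the same class as one who gets two levels better.

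Of the listed outcomes, this scale is the one that rates how the disease affects everyday life. A real benefit of the tube on function could therefore be reported as no effect because of the scoring. The analysis is also not fully fixed: two cuts and two methods stand side by side.

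**Working it through.** **1. Scale arithmetic (documents only).** With 1 as the best level, the largest possible improvement is the entry level minus 1. That is 0 at level 1, 1 at level 2, 2 at level 3 and 5 at level 6. A two-level improvement is therefore out of reach from levels 1 and 2. From level 2, a real one-level gain exists and is discarded. From level 1 there is no gain to discard.

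**2. The two cuts side by side.** Under the running text (2 or more, or not), a change of exactly two is a response. Under the table (more than 2, or less than 2), it belongs to neither class. The two give different data sets.

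**3. Is there a stated figure to reproduce?** No. The 47 per arm under Sample size is derived for the attack count. No power, effect or level distribution is given for the functional scale. I take 47 per arm and a two-sided 5% level (sidedness is not stated). Everything below is assumption.

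**4. Cost of a cut, latent-normal model.** Choose the shift that gives 80% power without a cut:

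d = (1.960 + 0.842) × √(2/47) = 0.578 SD.

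If a proportion p0 of controls passes the cut, then p1 = Φ(Φ⁻¹(p0) + d). With p̄ the mean of p0 and p1,

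power = Φ{[p1 − p0 − 1.96 √(2p̄(1−p̄)/47)] / √([p0(1−p0) + p1(1−p1)]/47)}.

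Example, p0 = 0.10: p1 = Φ(−1.282 + 0.578) = 0.241, and power = Φ[(0.1408 − 0.1520)/0.0762] = Φ(−0.147) = 0.442. The loss is 80 − 44 = 36 points.

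| Controls passing cut | Treated passing cut | Power with cut | Loss (points) |
|---|---|---|---|
| 5% | 14% | 33% | 47 |
| 10% | 24% | 44% | 36 |
| 15% | 32% | 51% | 29 |
| 20% | 40% | 55% | 25 |
| 30% | 52% | 59% | 21 |
| 40% | 63% | 60% | 20 |
| 50% | 72% | 59% | 22 |

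Starting from 90% power, the loss is 17 to 47 points.

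**5. Six-level simulation with floor and ceiling.** Assumed inputs: three entry-level mixes (low, levels 1 to 3; middle; high), mean control improvement 0, 0.5 or 1.0 level, SD 0.8 or 1.2, effect 0.5 or 0.7 level. That makes 3 × 3 × 2 × 2 = 36 settings, with 1,500 runs each. Improvement by two or more levels (likelihood-ratio test) was compared with ANCOVA on the level and with a rank test on change. Losses come from unrounded power.

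| Setting (mix, control improvement, SD, effect) | ANCOVA | Rank test | Cut at 2 or more | Loss vs ANCOVA / rank |
|---|---|---|---|---|
| Low, 0, 0.8, 0.7 (largest loss) | 95% | 93% | 47% | 49 / 47 |
| Middle, 0.5, 1.2, 0.7 | 72% | 68% | 45% | 27 / 23 |
| High, 1.0, 0.8, 0.7 (smallest loss) | 97% | 96% | 88% | 9 / 8 |

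Power was lost in all 36 settings: 9 to 49 points against ANCOVA and 8 to 47 against the rank test. The rank-test comparison has no baseline adjustment, so the loss does not come only from leaving out the inclusion level. With the table's cut (more than 2), power was 0 to 54%.

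**6. Direction pooled.** Simulations from a proportional-odds model used a placebo shift of 0.7 logits, baseline slope 1.0 or 1.5 per level, and 10, 25 or 40% entering at levels 1 to 2 (400 runs each).

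| Common odds ratio | Improved by 2 or more | Changed by 2 or more, either way | Ordinal, baseline-adjusted |
|---|---|---|---|
| 2.5 | 29–44% | 14–34% | 64–72% |
| 3.5 | 48–71% | 23–58% | 89–92% |

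**7. The linear alternative.** In similar runs (300 each), baseline-adjusted linear regression on the level had 57–68% power against 63–68% for ordinal regression at odds ratio 2.5, and 80–91% against 87–92% at 3.5. Ordinary least squares stood in for the bootstrap, and the plan does not state baseline adjustment.

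**The case against.** The strongest reply is that the plan already offers a way out. The table's linear alternative, read as regression of the level or its change, keeps one-level moves, and step 7 suggests it would recover most of the loss. That stands as far as it goes, so it would be wrong to infer that the plan contains only the binary analysis. But no condition says when the alternative replaces logistic regression. The same row still labels the outcome binary, and the running text commits only to the cut. Applied literally to the binary variable, a linear model would recover nothing.

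Four further inferences are tempting and are not supported:

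- *A fixed loss of a quarter to two fifths of power.* The documents give no inputs for this outcome. Even step 6 contains a pairing (71% against 89–92%) that puts the loss at 18 to 21 points.
- *Improvement lost for patients entering at level 1.* They are at the best level, so no analysis could credit them. The loss concerns level 2. How many enter there is unknown, and because the rule says change, these patients can still count by worsening.
- *No clinical rationale exists for two levels.* The article condenses a fuller protocol. What can be said is that the only reason it prints is the choice of model.
- *The trial's main conclusion is at risk.* The primary outcome is the attack count, and the sample size rests on that.

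A two-level responder is easy to explain to clinicians, and choosing it over an ordinal model is partly a matter of judgement. The full protocol or SAP may also settle direction and the trigger. Neither point removes the conflict between the two cuts.

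**Conclusion.** The concern holds as an inefficient and incompletely fixed analysis of one secondary outcome. Four things follow from the article alone: the printed reason does not require a cut; one-level changes, including level 2 to 1, score as no change; direction is undefined; and the text and table disagree on the cut while naming two methods without a rule for choosing.

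The size of the power loss does not follow from the article. With 47 per arm, two-sided 5%, and assumed entry levels, control improvement, spread and effect, it ran from about 8 to 49 percentage points when the cut is read as improvement by two or more. It was largest when few controls reach a two-level improvement. The primary conclusion is unaffected. This is a cheap improvement worth making before unblinding.

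**What to change.** Replace the functional-level rule in both the running text and the secondary-outcome table with one analysis: proportional-odds logistic regression of the level at 3 months on treatment group, with the level at inclusion as covariate, reported as a common odds ratio with 95% CI. Delete the untriggered alternative. Show the percentages improving by two or more levels and worsening by two or more levels separately, by arm, as description only. This also removes the conflict between the two cuts.

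Cost: analysis wording only, since both measurements are already collected and the model is standard software. The downsides are a proportional-odds assumption and an effect measure less familiar to clinical readers than a responder percentage, which the descriptive table partly offsets.
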